**10.2 Study of the microbiological flora**

Antibiotics can modify original endogenous flora of hospitalized patients. It can promote the growth of exogenous bacteria in these patients. A short course of antibiotics may represent a lower risk of disruption of bacterial flora in hospitalised patietns with equal clinical effectiveness.

**Objective:** study the changes in intestinal flora through pathological specimens (antibiotic resistance phenotype +/-genotypes).

**Method:** the study of the endogenous flora is based on the analysis of faecal flora taken by rectal swabs, on the identification of the species present at the beginning and end of treatment and the determination of their antibiotic susceptibility phenotype.

Identification of the character isogenic strains is to be conducted for some species (Pseudomonas aeruginosa, Klebsiella pneumoniae, Enterobacter aerogenes, Enterobacter cloacae, Staphylococcus aureus and Enterococcus faecalis) found in J0 J8, J15 and variation in sensitivity to antibiotics, as well as for pathogenic species which strains are identical to faecal strains (study of the bacterial Ecology: Appendix XIV).

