**5.2 Treatment**

All patients included in the study will be treated by a combination of antibiotics during the first 5 days (Beta-lactam + Aminoglycoside), then by monotherapy (Beta-lactam alone) for 3 or 10 days according to the group. The beta-lactam antibiotics will be administered in high doses during the first 3 days of treatment. Aminoglycosides will be administered as a single daily dose, with a loading dose administered on the first day of treatment. The patient will remain hospitalized (intensive care units or other units) for the duration of the treatment.

Definition :

- J0 = introduction of treatment whatever the time is
- J1 = first full day of treatment
- J4 = decrease in the dose of beta-lactam antibiotics, after 3 full days of treatment with high dose antibiotics; intermediate evaluation will be performed
- J6 = Stop aminoglycosides, after 5 full days of treatment
- J9 = Stop beta-lactam antibiotics in the "short" arm.
- J16 = Stop of the beta-lactam antibiotics in the "long" arm.
- J21 = Final evaluation.

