**8.3 Randomisation**

Is carried out in the final inclusion. It will be performed by the main investigator centre using a pre-defined centre randomization table. The assigned treatment arm is communicated by fax between 8 a.m. and 12 p.m., Monday to Friday and at the latest by D5.

1. **Methodology**

- **Pre-inclusion**
- verification of the criteria for inclusion (except bacteriological data) and exclusion
- realization of the BAL
- realization of 3 blood cultures
- simplified acute physiologic score: SAPSIIS II (Appendix VIII)(Appendix IX) Mc Cabbe score - score of organ failure (ODIN: Appendix X)
- -score of organ failure related to sepsis (SOFA: Appendix V)
- **Inclusion**
- verification of the bacteriological criteria for inclusion.
- **D0 of treatment**
- SAPS II (Appendix VIII) score
- score of organ failure (ODIN: Appendix X)
- score of organ failure related to sepsis (SOFA: Appendix V)
- **D1 of treatment**
- SAPS II (Appendix VIII) score
- score of organ failure (ODIN: Appendix X)
- score of organl failure related to sepsis (SOFA: Appendix V)
- rectal swabs
- **D4 of treatment**
- **decrease of dosages of beta-lactam - interim evaluation**

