**. D6 of Treatment**

- Stop Aminoglycoside

- **D9 of treatment**
- rectal swabs
- interim evaluation of healing
- **D16 of treatment**
- rectal swabs
- interim evaluation of healing
- **D leave intensive care or hospital if  21 days** : intermediate evaluation of healing

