**Appendix XIV : Study of bacteriological ecology changes (performed in some centers)**

In some centres, stool sampling is performed for each patient on the first day of treatment, and then at D8-D15. In addition, all bacteriological samples are retained.

Cultures. The rectal swab will be seeded on selective media (media of Chapman, Slanetz, Drigalski and agar Hyper-Agar). Usual bacteriological samples are treated according to standard protocols.

- Identification and antibiotics sensitivity phenotypes. For rectal specimens, all strains will be identified. Only the following species will be kept for 1 month: Pseudomonas aeruginosa, Enterobacter cloacae, Enterobacter aerogenes, Klebsiella pneumoniae, Staphylococcus aureus and Enterococcus faecalis. It will be performed a sensitivity by the method of diffusion agar (disk Pasteur TM, Kirby-Bauer method). The phenotype of resistance will be carried over to the following table:

Resistance Phenotype of bacteria isolated from rectal and pathological phenotype

| **Bacteria** | **Ps.aeruginosa** | **K.pneumoniae** | **E.aerogenes** | **E.cloacae** | **S.aureus** | **E.faecalis** |
| --- | --- | --- | --- | --- | --- | --- |
|  |  |  |  |  |  |  |
| Wild |  |  |  |  |  |  |
|  |  |  |  |  |  |  |
| Penicillinase |  |  |  |  |  |  |
|  |  |  |  |  |  |  |
| EBLS |  |  |  |  |  |  |
|  |  |  |  |  |  |  |
| Inducible Kephalosporinase |  |  |  |  |  |  |
|  |  |  |  |  |  |  |
|  |  |  |  |  |  |  |
| D2 |  |  |  |  |  |  |
|  |  |  |  |  |  |  |
| Meti-R |  |  |  |  |  |  |
|  |  |  |  |  |  |  |
| High level R |  |  |  |  |  |  |
| Kana-Genta |  |  |  |  |  |  |
|  |  |  |  |  |  |  |
| High level R. |  |  |  |  |  |  |
| Kana |  |  |  |  |  |  |

**Conservation of strains for genotyping:** rectal strains, all strains of the same species with a variation in sensitivity to antibiotics over time will be kept. For pathogenic strains, will be kept strains belonging to the species found in the stool. Strains will be kept in agar conservation.

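### Rectal-swab days differ between section 8, section 10.2 and Appendix XIV, and none of them secures a swab before the first antibiotic dose

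*Protocol*

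**What the plan says.** The flora study is a secondary objective (sections 3 and 10.2). Its aim is to describe how intestinal flora and resistance change, and its method rests "on the identification of the species present at the beginning and end of treatment and the determination of their antibiotic susceptibility phenotype". Three places give sampling days:

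- **Section 8**, in the day-by-day list after 8.3: rectal swabs appear under "D1 of treatment", "D9 of treatment" and "D16 of treatment". None is listed at pre-inclusion, where the BAL and blood cultures are taken, or at D0, where only severity and organ-failure scores are recorded.
- **Section 10.2**: strain typing covers certain species "found in J0 J8, J15 and variation in sensitivity to antibiotics".
- **Appendix XIV**, for participating centres: "stool sampling is performed for each patient on the first day of treatment, and then at D8-D15".

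Section 5.2 supplies the definitions: "J0 = introduction of treatment whatever the time is" and "J1 = first full day of treatment". It stops the beta-lactam at J9 in the short arm and at J16 in the long arm.

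**The concern.** A study of change under treatment needs a starting point that precedes treatment. This trial is well placed to obtain one: section 6.2 excludes patients who had antibiotics in the 3 days before diagnosis, surgical prophylaxis aside. The visit list nevertheless puts the first swab after treatment has begun, and a missed pre-dose sample cannot be recovered. A susceptible strain no longer detectable at D1 would be recorded as absent at the start. It could not then contribute to the sets of strains with changing susceptibility that Appendix XIV keeps for genotyping.

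Two further points follow from the wording. Centres working from different sections would collect samples at different stages of treatment. And a beginning-to-end comparison, read literally, ends on a different study day in each arm.

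**Working it through.** No sample-size or power figure bears on this point. The check sets the three schedules side by side and applies the section 5.2 definitions.

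| Source | First swab | Second | Third |
|---|---|---|---|
| Section 8 | D1 | D9 | D16 |
| Section 10.2 | J0 | J8 | J15 |
| Appendix XIV | first treatment day (J0 or J1 not said) | D8 | D15 (or D8-D15 as a window; not said) |

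**1. Size of the conflict.** Section 8 minus section 10.2: 1 − 0 = 1, 9 − 8 = 1, 16 − 15 = 1. The offset is exactly one day throughout.

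**2. Is it only a numbering habit?** Not within section 8. Its D4 (beta-lactam reduction) and D6 (aminoglycoside stop) match J4 and J6 in section 5.2, and it lists D0 separately from D1. Its D1 is therefore J1. If section 10.2 instead meant its J0 to be that same day, it would contradict section 5.2, and there would still be no pre-dose swab.

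**3. Exposure before a D1 swab.** J0 starts at any hour, so it contributes more than 0 and up to 24 h. J1 contributes 0 to 24 h, depending on when the swab is taken. The sum is more than 0 and up to about 48 h. The upper end needs a first dose just after midnight on J0 and a swab late on D1.

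**4. What the later days represent.** Both arms receive 5 days of combination, then monotherapy for 3 or 10 days: 5 + 3 = 8 and 5 + 10 = 15 full days.

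- J8 is the short arm's last full treatment day and J9 its stop day. Planned treatment is the same in both arms through J8, so a D8 or D9 swab carries almost no contrast in duration.
- J15 is the long arm's last full treatment day and J16 its stop day. By then the short arm is 15 − 9 = 6 or 16 − 9 = 7 days past its stop. This is the swab that contrasts the two durations.

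**5. End of treatment.** J16 − J9 = 7 days apart between arms.

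**6. Swabs that a pre-dose rule could waste.** Section 11.2 plans 350 pre-included and 280 included: 350 − 280 = 70, or 20%. This is a ceiling. Only some centres take part, and patients treated on the BAL result can be swabbed once inclusion is known.

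**The case against.** The strongest reply is that the trial compares 8 with 15 days, not antibiotics with none. Planned exposure before D1 is the same in both arms, so a D1 swab is a common reference taken well before the arms diverge. It blurs the description of change within patients but does not bias the randomised contrast. That stands, and it limits the point.

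It is also fair that J0 in section 10.2, and possibly the wording of Appendix XIV, leave room for a pre-dose swab. Room is not a requirement, however, and the visit list, which sets out the procedures day by day, starts at D1. Nor does the protocol show how far rectal flora is already altered by D1, so the size of the loss is unknown.

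A reader might infer more than the text supports:

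- **That the arms share no comparison day.** They do. No schedule distinguishes between arms, so both are swabbed on the same days.
- **That data from different centres could not be pooled.** A uniform one-day shift does not establish that, and nothing suggests it would differ by arm.
- **That the comparison is biased towards the short arm through shorter hospital exposure.** No section prescribes comparing D9 in one arm with D16 in the other, and the documents give no figure for such an effect. What remains is that section 10.2's wording permits that reading.

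Naming the comparison day might be left to an analysis plan. The conflicting sampling days and the missing pre-dose rule cannot be, because they govern what is collected.

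**Conclusion.** The point holds in a limited form. The three sections disagree on swab days, by one day at every time point between sections 8 and 10.2, with an ambiguous third wording in Appendix XIV. Under the visit list the first swab always follows the start of antibiotics, by more than 0 and up to about 48 h, and no section requires an earlier one. The within-patient description of flora change therefore has no secured untreated baseline. The between-arm contrast is affected less. Separately, the end of treatment named in section 10.2 falls 7 days apart in the two arms, although common swab days exist.

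This rests on reading D and J as the same day count, which section 8's own D4 and D6 entries support. The passages should be reconciled. The matter is a secondary objective run in some centres and does not touch the primary endpoint.

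**What to change.** 1. Write one set of swab days identically in section 8, section 10.2 and Appendix XIV, and make clear that the later swabs are two fixed days, not a window.
2. Require the first swab before the first antibiotic dose: at the BAL for patients treated immediately, and on D0 before that dose for those treated on the BAL result.
3. Make the between-arm comparison on the same late study day in both arms (D15 or D16, as reconciled), rather than at each arm's end of treatment.

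This changes sampling only, not treatment, and the number of swabs per included patient stays the same. There are three costs:

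- Swabs taken at the BAL are wasted for pre-included patients who are not finally included: at most 70 of 350, and fewer in practice.
- A swab at the BAL is a research procedure before final inclusion, so section 8.1 must list it.
- Late swabs may be missing more often in the short arm. Section 5.2 requires hospital stay only while treatment lasts, and section 7.2.2 foresees a telephone interview at D21 for patients at home. Missing late swabs should be reported by arm.

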**10.3 Economical study**

Little data is currently available on the economic impact of the duration of antibiotic therapy. A hypothesis is that the cost of a defined treatment is proportional to its length. However, two factors directly related to the duration of treatment may alter the overall cost of support for the infection (25): the failure of the first line treatment and/or the emergence of resistant bacteria (antibiotic pressure). The additional costs then correspond to the treatment of the infections and/or complications (septic shock...). These additional costs are rarely evaluated (23). It therefore appears necessary to compare the costs of two therapeutic strategies (8 days versus 15 days of antibiotic treatment). Such a study will evaluate the influence of the duration of treatment on the different costs of management of nosocomial pulmonary disease and its complications through analysing the costs of hospitalization, drugs, devices, and other medical expenditures.

**Method** : Study cost-identification, from the point of view of the hospital will be collected from D0 to D21 and the direct costs attributable to nosocomial pneumonia and its complications. Data will be collected and the costs will be analysed for each of the two groups:

**# Hospital fees** : for a nosocomial infection, it is difficult to discern the hospitalization related to infection and that related to the initial pathology. Hospitalization in connection with the lung disease and its complications will be calculated by counting the number of days during which the patient will be treated by anti-infective treatments. The costs will be calculated through the analytical accounting of a centre of reference.

**# Treatments** : will be taken into account for the specific treatment of lung disease, pulmonary and extra-pulmonaires infections and, where appropriate, of septic shock. Costs identified until D21 will include:

- anti-infective (antibacterial and antifungal)

- for septic shock: a Swan-Ganz probe insertion: hemodialysis or Hemofiltration: specific treatments

- management of the complications caused by treatment (e,g, pseudomembranous colitis) these costs will be calculated from the "markets" 1996 price at the centre of reference. For hemodialysis or Hemofiltration, a daily average cost will be calculated by a reference centre.

**# Investigations**: These will be taken into account as the specific investigations related to lung disease and infections, namely:

- radiological examinations (x-rays and scanners)

- bacteriological examinations

- assays of antibiotics.

These costs will be calculated from the nomenclature of the acts in force since 1996.

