**11.2 Number of patients**

The calculation of the number of patients was carried out under the following conditions: the equivalence is accepted up to a maximum variation of 10% between clinical cure rates. The rate of successful treatment for the usual duration of antibiotic therapy (15 days) is between 80 and 90%.

Patients are randomized after the result of the BAL: it is estimated that 20% of patients pre-included may not be included permanently. This produces a risk equal to 0.20. The number of subjects to be included must be a minimum of 275 and maximum of 350 for the initial value of the rate of cure and the risk (chosen, as indicated in the table below):

| %  cured |  |  | n/group | N pre included | Total included |
| --- | --- | --- | --- | --- | --- |
| 0.90 | 0.05 | 0.20 | 110 | 275 | 220 |
| 0.85 | 0.10 | 0.20 | 110 | 275 | 220 |
| 0.80 | 0.10 | 0.20 | 140 | 350 | 280 |

The number of patients selected for the study is 350.

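### Section 10.3 counts hospital days as days on anti-infectives, which gives the 8-day arm a built-in 7-day head start in the hospitalisation cost

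*Protocol*

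**What the plan says.** Protocol section 10.3 sets out to "compare the costs of two therapeutic strategies (8 days versus 15 days of antibiotic treatment"). It starts from a premise, "A hypothesis is that the cost of a defined treatment is proportional to its length", and then names two things that could break it: failure of first-line treatment and the emergence of resistant bacteria. The viewpoint is the hospital's. On scope, it says that data "will be collected from D0 to D21 and the direct costs attributable to nosocomial pneumonia and its complications".

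For the hospitalisation item, the section notes that "it is difficult to discern the hospitalization related to infection and that related to the initial pathology". Its answer is a counting rule: hospitalisation linked to the lung disease and its complications "will be calculated by counting the number of days during which the patient will be treated by anti-infective treatments". Those days are priced from a reference centre's accounts. Drugs, septic shock care, treatment complications and investigations are costed as separate items.

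Section 5.2 fixes the exposure. All patients receive 5 days of combination therapy, "then by monotherapy (Beta-lactam alone) for 3 or 10 days according to the group". It also says: "The patient will remain hospitalized (intensive care units or other units) for the duration of the treatment".

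Appendix VII, the daily follow-up sheet, records alive or dead, ICU yes or no, and transfer to ward or home.

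**The concern.** The outcome used for hospital cost is, for most of its length, the treatment that was assigned. An uncomplicated patient is charged 8 or 15 hospital days because of the randomisation, whatever the real length of stay. The proportionality that section 10.3 puts forward as a hypothesis is thus built into the measure meant to examine it.

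The rule also leaves days out. A patient who recovers slowly and stays on without anti-infectives adds nothing to the count, so that form of extra cost after a short course cannot appear.

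At stake is the reading of one secondary objective. A reported hospital saving for the short arm could be mostly the counting rule. The primary comparison of cure rates is not affected.

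**Working it through.** **Inputs**
- Assigned course: 5 + 3 or 5 + 10 days (section 5.2).
- Stop days: J9 and J16, with J1 the first full day (section 5.2).
- Costing window: to D21 (section 10.3).
- Planning cure rate: "The rate of successful treatment for the usual duration of antibiotic therapy (15 days) is between 80 and 90" per cent (section 11.2), with a 10-point equivalence margin (same section).
- Not in the protocol: unit costs, superinfection rate, length of retreatment. These are assumed below or left out.

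**1. Reproduce the plan's durations.** 5 + 3 = 8 and 5 + 10 = 15. The stop days agree: J1 to J8 is 8 full days and J1 to J15 is 15.

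**2. Built-in gap, uncomplicated course.** 15 − 8 = 7 counted hospital days; 7/15 = 46.7%. If the partial day J0 is counted too, it is 9 versus 16: still 7 days, and 7/16 = 43.8%.

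**3. Same real stay, two measures.** Take two patients, one per arm, both in hospital from D1 to D21 without complications.

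| Measure | Short | Long | Difference |
|---|---|---|---|
| Actual bed-days | 21 | 21 | 0 |
| Section 10.3 count | 8 | 15 | 7 |

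**4. How much retreatment would cancel the gap?** Days left to D21 after the course are 21 − 8 = 13 (short) and 21 − 15 = 6 (long). With no retreatment in the long arm, the break-even share of short-arm patients is 7 divided by the days of retreatment:
- 13 days (the maximum): 7/13 = 54%
- 10 days: 7/10 = 70%
- 7 days: 7/7 = 100%

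**5. The protocol's own worst accepted case.** Take 80% cure in the long arm and 70% in the short arm, so 20% and 30% failure. Assume every failure is treated on all days to D21.
- Short: 8 + 0.30 × 13 = 11.9
- Long: 15 + 0.20 × 6 = 16.2
- Gap: 4.3 days, 4.3/16.2 = 27%
- With no long-arm retreatment: 15 − 11.9 = 3.1 days, 3.1/15 = 21%

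The short arm fails 10 points more often and is still charged fewer hospital days.

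**6. Other things that narrow the gap (assumed ranges).**
- If 10% to 30% of each arm die or fail before D9 with equal counted days, the gap is 0.9 × 7 = 6.3 down to 0.7 × 7 = 4.9 days.
- If a superinfection is treated throughout D9 to D15 in the same share of both arms, it adds days only in the short arm, because the long arm is already on treatment. At 10%, 30% and 50% the gap is 15 − (8 + 7 × share) = 6.3, 4.9 and 3.5 days. It reaches 0 only at 100%.

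No monetary figure can be computed.

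**The case against.** A reader might infer that the economic study can only conclude that the short course is cheaper. The protocol does not support that. The rule counts days on any anti-infective, so retreatment for failure or superinfection adds days, and the short arm has 13 days in which to collect them against 6. The separately costed items are not tied to 8 or 15 days and could offset the difference in total cost. Nor can it be said that hospitalisation dominates the total, because no unit costs are given. And section 10.3 states proportionality in order to look for departures from it.

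The rule also has a stated reason: separating infection-related stay from stay for the initial illness is hard. That is a fair problem in an uncontrolled cost study. In a randomised comparison, days due to the initial illness balance between arms in expectation, so the difference in all bed-days needs no attribution rule.

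Finally, section 5.2 keeps patients in hospital while on treatment, so part of the 7 days may be real for patients otherwise ready to leave. That stands. Actual bed-days would capture that part; the section 10.3 count charges the same 7 days to patients who would have stayed anyway.

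**Conclusion.** The point holds for the hospitalisation component, as a head start and not as a certainty about total cost. The size is 7 counted days (47%) for patients who complete an uncomplicated course, even with identical real stays. Retreatment, superinfection and early death reduce it. In the scenarios tried at the planning failure rates, 3.1 to 4.3 days remain, under the assumption that every counted failure is treated to D21. Cancelling it by retreatment alone needs at least 54% of the short arm treated on every remaining day. Whether the other cost items would offset it in money cannot be determined from the protocol.

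This is a rule that the protocol states, not a detail left for later. It concerns a secondary objective and should be corrected before the cost analysis.

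**What to change.** In section 10.3, make the main hospital cost the actual ICU and ward days from D0 to D21 for every randomised patient. Take them from the Appendix VII daily sheet, compare them by assigned arm, and price them at the reference centre's daily cost. Keep the anti-infective-day count as a sensitivity analysis or as a drug-use result.

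Three things should be stated with it:
- The target changes from cost attributable to pneumonia to all-cause hospital cost to D21, and estimates will be more variable because the underlying illness is included.
- The section 5.2 rule on staying in hospital during treatment still makes part of any bed-day difference protocol-driven.
- Death shortens counted stay, so an arm with more early deaths can look cheaper. Deaths should be reported by arm beside the costs.

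The change needs no new data item, visit, sample size or treatment change, since location and vital status are already on the sheet. Its price is a redefined cost target and less precision.
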